### Data management

2.13

During each study visit, patient demographics and all clinical data will be recorded and maintained in physical medical record folders. Data will then be entered into Epidata software to centralize all study data. The data management process will adhere to regulatory requirements outlined in the Good Clinical Practice (GCP) guidelines and the Technical Guidelines for Clinical Trial Data Management, ensuring the authenticity, completeness, accuracy, and traceability of data.

### Quality control in research

2.14

Investigators shall fulfill their respective responsibilities and strictly adhere to the clinical research protocol, employing standard operating procedures. All relevant observations and findings must be verified to ensure the implementation of the clinical research quality control and quality assurance system. Investigators must provide necessary training to all personnel involved in the clinical research, explaining relevant materials, operational standards, and responsibilities to ensure data is recorded truthfully, accurately, completely, promptly, and lawfully in medical records and CRFs. Subject allocation in clinical research must follow the randomized allocation plan specified in the study design. The treatment group coding for each subject should be maintained as a blinded baseline by both the statistical unit and the investigator. Monitors shall follow standard operating procedures to oversee protocol compliance, confirm the accuracy and completeness of all data recording and reporting, and ensure CRFs are correctly completed and consistent with source documents. Auditors shall conduct systematic reviews of clinical research activities and documentation to evaluate compliance with the protocol, SOPs, and relevant regulatory requirements. All laboratory test data in clinical research must be accurate and either documented in the case report form or supported by original report copies attached thereto. Medical statisticians shall incorporate study data into reports completely and without error. All steps involving data management must be documented to facilitate verification of data quality and implementation processes.

### Data analysis and statistical methods

2.15

SPSS 24.0 software will be used to perform statistical analysis on the collected data. All statistical tests will be two-tailed, with a *P*-value ≤ 0.05 indicating statistical significance for the tested difference. Descriptive analysis: Categorical indicators will describe the number and percentage of cases in each category. Quantitative indicators will be described using mean, standard deviation, maximum value, minimum value, median, lower quartile (Q1), and upper quartile (Q3). Comparisons between two groups of general characteristics will be analyzed using appropriate methods based on the type of indicator. For quantitative data, between-group comparisons will employ paired t-tests or Wilcoxon signed-rank tests. For categorical data, chi-square tests or exact probability methods will be used. For ordinal data, Wilcoxon signed-rank tests or the Mann–Whitney U (MWU) test will be applied. Age, atrial fibrillation status and estimated glomerular filtration rate will be recorded at baseline and examined in covariate-adjusted and sensitivity analyses because these factors can materially alter NT-proBNP concentrations. Time to first event will be displayed with Kaplan–Meier curves, compared by the log-rank test, and modeled using Cox regression to estimate hazard ratios (HRs) with 95% confidence intervals. Event counts and recurrent rehospitalizations will be summarized descriptively by group.

The Full Analysis Set (FAS) followed the intention-to-treat principle, including all randomized subjects who received at least one dose of the study drug, with exclusions limited to major protocol violations, no study drug exposure, or complete lack of post-randomization data. The per-protocol set (participants with ≥80% adherence, primary endpoint data and no major protocol violation) will support sensitivity analyses, and the safety set will include all randomized participants who received at least one dose and had a safety assessment. For missing co-primary endpoint data, the prespecified conservative worst-case approach will be used in the primary FAS analysis. Missing data amount, reasons and patterns will be reported by group. Multiple imputation under a missing-at-random assumption will be used as a sensitivity analysis, with additional best/worst-case analyses to evaluate departures from that assumption.

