# Long-term efficacy and impact on rehospitalization of Qishen granules in patients with hypertension and heart failure with reduced ejection fraction: a multicenter, randomized, double-blind, placebo-controlled trial protocol

**DOI:** 10.3389/fcvm.2026.1897966

**Published:** 2026-09-07

**Keywords:** Chinese medicine, clinical protocol, HFREF, hypertension, RCT - randomized controlled trial

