### Confirmation of case count

2.3

The sample size was calculated based on the expected reduction in serum NT-proBNP levels. Consistent with previous studies demonstrating that a > 30% reduction in NT-proBNP is associated with significantly better prognosis compared to stable or rising levels, efficacy was defined as a > 30% decrease from baseline (11). Based on preliminary research data, the efficacy rates of QSG and placebo after 12 weeks of intervention in chronic heart failure were 50% and 32%, respectively (9). Furthermore, pre-experimental studies demonstrated that QSG significantly improved cardiac function, cardiac structure, and factors related to myocardial hypertrophy in mice with transverse aortic constriction (TAC)-induced heart failure. Therefore, this study projected an efficacy rate of 53% for QSG and 33% for placebo. Given a type-I error rate of *α* = 0.05 and a type-II error rate of *β* = 0.2, and accounting for a 15% dropout rate, the required sample size was calculated using the two-sample comparison of proportions in *PASS* (version 21.0.3) software. This yielded 110 patients per group, totaling 220 cases for both groups.

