#### Secondary outcome

2.12.2

The following parameters were obtained via echocardiography: Left ventricular ejection fraction (LVEF), Left ventricular end-diastolic diameter (LVEDD), Left ventricular end-systolic diameter (LVESD), Interventricular septal thickness (IVS), Left ventricular posterior wall thickness (LVPW), Left ventricular short-axis fractional shortening (FS), Early diastolic peak mitral flow velocity/ late diastolic mitral flow peak (E/A), and early diastolic mitral flow velocity/tissue Doppler early diastolic annular velocity (E/e’).NYHA Functional Class: The NYHA classification categorizes the impairment of cardiac function into four levels based on the level of activity that induces heart failure symptoms (12).Kansas City Cardiomyopathy Quality of Life Questionnaire (KCCQ): KCCQ is a scoring tool used to assess the health status of patients with heart failure. It comprises 23 questions across seven domains: physical limitations, self-assessment, symptoms, self-awareness, psychological aspects, social functioning, and clinical assessment. Completion typically takes 4–6 min. Each question is scored out of 100 points, with higher scores indicating better quality of life.Quantification Table for Toxic Pathogenic Factors in Heart Failure (https://www.cacm.org.cn/2024/12/02/30894/).

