#### Long-term follow-up outcomes and event adjudication

2.12.4

At weeks 26 and 52, investigators will collect the number and dates of heart-failure rehospitalizations and major cardiovascular events through scheduled contact, participant/family interview and review of hospital source records. Heart-failure rehospitalization is defined as an unscheduled admission for a primary diagnosis of worsening heart failure lasting >24 h, supported by new/worsening symptoms and signs and intensification of heart-failure therapy. All-cause rehospitalization is any unscheduled inpatient admission meeting the same duration rule, irrespective of cause. Cardiovascular events include cardiovascular death, nonfatal myocardial infarction, nonfatal stroke, resuscitated cardiac arrest, malignant arrhythmia and heart-failure rehospitalization. A blinded clinical endpoint committee, composed of three cardiologists blinded to treatment allocation, will adjudicate events from source documents. Disagreements will be resolved by consensus or by a fourth senior adjudicator. Only committee-adjudicated events will be used in the primary analyses of rehospitalization and cardiovascular outcomes.

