NYHA cardiac function classification serves as a widely accepted indicator for assessing impaired cardiac function (19, 20). Echocardiography accurately reflects ventricular remodeling and cardiac function status (21), making it one of our secondary outcome measures. Additionally, this study comprehensively evaluated patients’ living conditions, social quality, and physical changes. Therefore, the KCCQ and the Heart Failure Toxic Syndrome Quantification Scale were also considered as secondary outcome measures.

This study involves multiple participating institutions, making quality control one of our primary challenges. We established Standard Operating Procedures (SOP) and provided extensive training to all investigators/physicians prior to patient recruitment. Through initial, supplemental training, and ongoing review, we ensured proper execution of SOP to guarantee data collection quality. Furthermore, we prioritized patient communication to ensure all participants had a thorough understanding of the trial, enabling strict adherence to requirements and attendance at all scheduled appointments.

This study design strictly adheres to the CONSORT guidelines employing a multicenter, randomized, double-blind, placebo-controlled trial design to minimize bias (22). The sample size calculation is scientifically sound, with a follow-up period extending to 52 weeks, enabling thorough assessment of long-term efficacy and safety outcomes. Furthermore, we incorporated readmission rates as a late-stage follow-up indicator, directly linking to health economics metrics, thereby demonstrating strong clinical and practical significance. We anticipate this clinical trial will provide high-level evidence-based medical evidence for the application of traditional Chinese medicine in the field of hypertension-related heart failure.

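### The titled rehospitalization question has three overlapping event outcomes, no named lead, and a P ≤ 0.05 rule that applies to each of them whatever the primary result

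*Protocol article*

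**What the plan says.** The title announces "Long-term efficacy and impact on rehospitalization of Qishen granules in patients with hypertension and heart failure with reduced ejection fraction". The outcome lists do not follow it. Section 2.12.1 gives the NT-proBNP responder rate at week 12 as the main primary outcome, with the six-minute walk test beside it. Section 2.12.2 lists echocardiography, NYHA class, KCCQ and the toxic-syndrome scale as secondary. Rehospitalization is in neither list, and the abstract also mentions it apart from both.

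It appears in section 2.12.4, which defines three event outcomes collected at weeks 26 and 52:
- heart-failure rehospitalization;
- all-cause rehospitalization;
- a composite of cardiovascular events, one component of which is heart-failure rehospitalization.

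The same section says: "Only committee-adjudicated events will be used in the primary analyses of rehospitalization and cardiovascular outcomes". It does not say which of the three answers the question in the title, or at which horizon.

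Section 2.15 sets the decision rule: "All statistical tests will be two-tailed, with a *P*-value ≤ 0.05 indicating statistical significance for the tested difference". It compares time to first event by log-rank test and Cox regression without naming the event. Event counts and recurrent rehospitalizations are descriptive only. The sample size in 2.3 rests on NT-proBNP response alone.

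**The concern.** A question placed in the title needs one outcome that answers it and a rule for when the answer counts. The article fixes neither. It offers three definitions that share many events but can disagree, leaves the tested event unnamed, and applies a significance rule that exempts no outcome and depends on no other result.

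Two things are at stake. First, which event outcome carries the rehospitalization claim could be settled after the results are known, and the error rate of that claim is then above 5%. Second, the claim does not depend on the primary outcome. The trial could fail on NT-proBNP, the only outcome it was sized for, and still report a statistically significant effect on rehospitalization.

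**Working it through.** **The plan's own figure.** Section 2.3 states that "this study projected an efficacy rate of 53% for QSG and 33% for placebo", with alpha 0.05, beta 0.2 and 15% dropout. With unpooled variance:

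n = (1.960 + 0.842)² × (0.53×0.47 + 0.33×0.67) / 0.20² = 7.85 × 0.4702 / 0.04 = 92.3, so 93 per group; 93 / 0.85 = 109.4, so 110 per group.

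This matches the stated 110 and 220. The calculation uses the full two-sided 0.05 for NT-proBNP response and contains no event outcome.

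**Which tests can yield a rehospitalization claim.** Two outcomes are rehospitalization outcomes. The composite makes three, since heart-failure rehospitalization is one of its components. I count one test per outcome at week 52.

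**Bounds.** If QSG has no effect and each test is run at 0.05, the chance of at least one P ≤ 0.05 is at most about:
- two independent tests: 1 − 0.95² = 9.8%;
- three independent tests: 1 − 0.95³ = 14.3%.

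If the outcomes coincided completely it would be 5%. The truth lies between, because the outcomes share events. For two normal test statistics with correlation 0.6, 0.7 and 0.8, the chance is 8.8%, 8.4% and 7.8%.

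**Simulation of the overlap.** The article gives no event rates, so all rates here are assumptions. I took 110 per arm, no treatment effect, exponential times, censoring at week 52 and two-sided log-rank tests, with 20,000 replicates. The composite is the earlier of heart-failure rehospitalization and another cardiovascular event. All-cause rehospitalization is the earlier of heart-failure rehospitalization and another admission.

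| Assumed one-year risk: HF rehospitalization / other CV event / other admission | Two rehospitalization outcomes | All three |
|---|---|---|
| 15% / 6% / 12% | 8.1% | 10.4% |
| 20% / 8% / 15% | 8.5% | 10.7% |
| 30% / 10% / 20% | 8.0% | 10.2% |

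The correlation between the two rehospitalization statistics was 0.72 to 0.75, which agrees with the normal calculation. If the other cardiovascular events also count as admissions, the figures are 8.4% to 9.0% and 10.0% to 10.6%. Simulation error is about 0.2 percentage points.

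Against 5% for a single named outcome, this is 8/5 = 1.6 times for two outcomes and 10/5 = 2 times for three.

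**After a fixed order.** If one named event outcome is tested at 0.05 only when the primary outcome is met, the chance of a false claim on it is at most 5%. If QSG has no effect on anything, a false rehospitalization claim needs two false positives in sequence. The sample size of 220 does not change.

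**The case against.** The strongest objection is scope. A testing order for secondary outcomes is commonly left to the SAP, which is not shown, and a two-sided 0.05 criterion is a conventional per-test statement. That stands for the 11 measures of 2.12.2 (eight echocardiographic, plus NYHA class, KCCQ and the syndrome scale), and the absence of an order among them is no finding in itself. It does not cover the event outcomes. There the article itself fixes a title, three definitions, an unnamed tested event and a rule for all tests.

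Several other points limit the concern:
- The outcomes are tiered by heading, and the Discussion treats readmission as a late follow-up indicator. This is true, but no testing rule follows from the headings.
- The reference in 2.12.4 to primary analyses most naturally means the main analysis of those outcomes. It does not show that they were promoted to primary endpoints.
- Event counts and recurrent rehospitalizations are not tested, so not every event analysis falls under the rule.
- The article does not say that three log-rank tests will be run. That number is inferred from the three definitions.
- The Discussion's statement "We anticipate this clinical trial will provide high-level evidence-based medical evidence" is a general hope for the trial. It is not a plan to claim a rehospitalization effect after a failed primary outcome.

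A reader might infer that the rehospitalization claim could come from any of 8 + 3 + 3 = 14 tests, with a false-positive chance of 35% at an assumed correlation of 0.5 (51% if independent). The documents do not support this, because echocardiography, NYHA class, KCCQ and the syndrome scale cannot yield a rehospitalization claim. A reader might also count weeks 26 and 52 as separate tests, which gives about 15% to 17% for six tests. The article describes those weeks as collection points and states no separate week-26 test.

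**Conclusion.** The concern holds for the event outcomes. The question in the title has no lead outcome or deciding horizon, and the text lets any of the three definitions be called significant at full alpha even if NT-proBNP fails. The inflation is moderate: about 8% for the two rehospitalization outcomes and about 10% for all three at week 52, instead of 5%. These figures assume no effect of QSG, one test per outcome, 110 per arm without loss to follow-up, and the event rates shown. They move little across those rates. The missing link to the primary outcome does not depend on any of these assumptions. The finding does not extend to the absence of an order among the secondary measures.

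**What to change.** In 2.12.4, name one key long-term outcome and its horizon, for example time to first adjudicated heart-failure rehospitalization through week 52. In 2.15, name that event in the log-rank and Cox sentence. Limit the P ≤ 0.05 significance claim to the primary outcome and, after it in a fixed order, this key outcome. State that P values for the other event outcomes and for the secondary outcomes are nominal and will be reported with estimates and 95% confidence intervals.

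This takes a few sentences before unblinding, with no new data, patients or change in sample size. The cost is that the sponsor gives up formal significance claims for the remaining outcomes, and for rehospitalization if the primary outcome is not met. If the sponsor does not want a confirmatory rehospitalization claim at all, it is enough to state that all event and secondary P values are nominal; the title should then not be read as promising such a claim.

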### Design

2.2

This study is a randomized, double-blind, placebo-controlled, parallel-group, multicenter clinical trial supported by the Key Research and Development Program of the Ministry of Science and Technology in China. It was conducted among patients with hypertension complicated by HFrEF. The study was conducted simultaneously at Guang'anmen Hospital of China Academy of Chinese Medical Sciences, Affiliated Hospital of Shandong University of Chinese Medicine, Langfang People's Hospital, Weifang Hospital of Traditional Chinese Medicine, Affiliated Hospital of Xinxiang Medical University, Beijing Changping District Hospital of Traditional Chinese Medicine, Shanxi Provincial Hospital of Traditional Chinese Medicine, China-Japan Friendship Hospital of Jilin University, Linyi Hospital of Traditional Chinese Medicine, Chaoyang Central Hospital, and Yantai Mountain Hospital, enrolling a total of 220 patients. After providing written consent, individuals with hypertension and HFrEF were randomly assigned to receive QSG or placebo for 12 weeks. Standardized treatment followed medication regimens specified in 2017 ACC/AHA/AAPA/ABC/ACPM/AGS/APhA/ASH/ASPC/NMA/PCNA Guideline (10) and the 2022 AHA/ACC/HFSA Heart Failure Management Guidelines (3). Drug types and doses were fixed (unless contraindicated or intolerable). Figure 1 illustrates the study flowchart.

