### Randomized design and blind method

2.9

This study employed stratified block randomization, with research centers as the stratification factor. The randomization table was generated by a statistician not involved in the study's statistical analysis using the PLAN procedure in SAS software. Samples were assigned according to group codes at a 1:1 ratio (Group A:Group B). Parameters such as block length and initial seed number, along with the randomization table itself, served as the primary blinding mechanism. The treatment assignments (experimental group, control group) corresponding to each group code constituted the secondary blinding mechanism. Both primary and secondary blinding layers were prepared in duplicate, sealed in opaque envelopes, and stored separately at the study coordinating institution and the sponsor. After screening and eligibility confirmation at each center, subjects were assigned random numbers sequentially based on enrollment timing and the center's allocated random number range. Medication corresponding to the assigned random number was then dispensed.

This study employs a double-blind design, meaning investigators, subjects, and all trial personnel remain blinded throughout the clinical trial. On-site drug blinding is guided by personnel from a statistical unit not involved in this study. The sponsor arranges for individuals unrelated to this trial to affix the pre-assigned drug codes onto labels. After packaging, each subject's medication will bear a unique drug code label corresponding to the drug code in the randomization table, which remains unchanged throughout the trial. Blinding records are maintained throughout the blinding process.

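### Paired t-tests and Wilcoxon signed-rank tests are named for between-group comparisons of quantitative data, but the two arms are independent and unmatched

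*Protocol article*

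**What the plan says.** The test for quantitative data is given in the protocol article, section 2.15 (Data analysis and statistical methods): "For quantitative data, between-group comparisons will employ paired t-tests or Wilcoxon signed-rank tests". The sentence just before it reads: "Comparisons between two groups of general characteristics will be analyzed using appropriate methods based on the type of indicator". The rules for the other data types follow directly: "For categorical data, chi-square tests or exact probability methods will be used", and "For ordinal data, Wilcoxon signed-rank tests or the Mann–Whitney U (MWU) test will be applied".

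On the design, section 2.2 says: "This study is a randomized, double-blind, placebo-controlled, parallel-group, multicenter clinical trial". Section 2.9 says: "This study employed stratified block randomization, with research centers as the stratification factor", with 1:1 allocation of individual patients. The article describes no matching of patients and no crossover.

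On the outcomes, section 2.12.1 defines the main primary outcome as the binary NT-proBNP responder rate at week 12. The Abstract and the Discussion also count the six-minute walk test as primary. Section 2.12.2 lists the echocardiographic parameters, NYHA class, KCCQ and the toxin quantification table as secondary.

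**The concern.** A paired t-test or signed-rank test works on differences within natural pairs. Between two independently randomized arms there are no such pairs. An analyst who follows the sentence has two options:

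- Pair QSG and placebo patients arbitrarily.
- Test before against after within each arm, which is not a comparison between arms.

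If the sentence covers efficacy outcomes, it is the only unadjusted test the article names for quantitative ones. That would include walk distance, a primary outcome, if it is analysed as a quantity. The article would then give no usable unadjusted test for those comparisons, and the choice would have to be made later.

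**Working it through.** **1. The plan's own figure.** Inputs from section 2.3: responder rates 53% and 33%, alpha 0.05 (two-sided, section 2.15), beta 0.2, dropout 15%. The unpooled two-proportion formula gives

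n = (1.960 + 0.842)² × (0.53×0.47 + 0.33×0.67) / 0.20² = 7.849 × 0.4702 / 0.04 = 92.3, so 93 per arm.

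93 / 0.85 = 109.4, so 110 per arm, as stated. This calculation treats the arms as independent samples and concerns a binary endpoint. The choice of test for quantitative data does not enter it.

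**2. Literal reading: pairing across arms.** With n per arm, the paired statistic is t = d̄ / (s_d/√n). The mean difference d̄ equals the difference in arm means however patients are paired. With equal SDs, s_d² = 2s²(1 − r), where r is the sample correlation that the chosen pairing happens to produce. So the paired t is the independent-samples t multiplied by 1/√(1 − r), and r is pure accident.

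Under random pairing r has standard error 1/√(n − 1). Taking 94 per arm (110 × 0.85 = 93.5, rounded up), this is 1/√93 = 0.104, so 95% of pairings give r between about −0.203 and +0.203. The multiplier then runs from 1/√1.203 = 0.912 to 1/√0.797 = 1.120.

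Take a dataset with independent-samples p = 0.067 (t = 1.845 on 186 df). The paired t runs from 1.845 × 0.912 = 1.68 to 1.845 × 1.120 = 2.07 on 93 df, so p runs from about 0.096 to 0.041.

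Simulation on one such dataset (normal data) agrees:

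| Test | p-value |
|---|---|
| Independent-samples t | 0.067 |
| Paired t, 5,000 random pairings, full range | 0.022 to 0.118 |
| Paired t, central 95% of pairings | 0.042 to 0.095 |
| Mann-Whitney U | 0.101 |
| Signed-rank, 2,000 random pairings, central 95% | 0.039 to 0.179 |

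The same data fall on either side of 0.05 depending on file order. With 94 and 90 patients the paired test cannot be run at all.

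Over 20,000 simulated trials with no treatment effect and equal arms, the paired t-test rejected in 5.06% and the independent t-test in 5.08%. The literal fault is therefore arbitrariness or non-computability, not an excess of false positives.

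**3. Other reading: before-after tests within each arm.** This is an illustration only. The standardized change is an assumption, since the article gives none. With 93 per arm and the same true change d (in SD of change) in both arms, each arm's test has noncentrality d√93. If p is its power, the chance that QSG is significant and placebo is not is p(1 − p).

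| d (assumed) | Power per arm, p | p(1 − p) |
|---|---|---|
| 0.10 | 0.16 | 0.13 |
| 0.15 | 0.30 | 0.21 |
| 0.20 | 0.48 | 0.25 |
| 0.25 | 0.66 | 0.22 |
| 0.30 | 0.82 | 0.15 |

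With no difference between arms, the pattern appears in about 13% to 25% of trials. Two within-arm p-values do not compare QSG with placebo.

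**4. What the sentence does and does not reach.** The responder rate is categorical and falls under the chi-square or exact test. Event times have Kaplan-Meier, log-rank and Cox methods. For quantitative outcomes, section 2.15 mentions covariate-adjusted and sensitivity analyses, motivated by factors that alter NT-proBNP, but names no model.

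**The case against.** The strongest case on the other side has four parts.

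- **Scope.** The preceding sentence is about general characteristics, so the list of tests may concern baseline comparisons only. This stands as an ambiguity: coverage of efficacy outcomes is the likelier reading, because no other unadjusted test is named for them, but it is not stated. It does not rescue the sentence, since paired tests are equally wrong for baseline tables.
- **Walk distance.** Section 2.12.1 sorts it into three ordered bands. An ordinal analysis, for which Mann-Whitney U is available, is therefore possible. This also stands: the primary outcome is touched only if distance is analysed as a quantity.
- **Ordinal data.** That sentence names a valid test and does not say that it concerns comparisons between groups. The signed-rank option could be meant for within-arm change in NYHA class. The fault here is lack of clarity rather than a plain error.
- **A drafting slip.** Independent-sample tests were probably intended. That is plausible, but the article names a specific wrong test for a specific purpose. An unseen analysis plan may be right, and this text would still need correcting.

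A reader might also infer that the plan carries a false-positive risk of up to 25%, against the 2.5% in QSG's favour that a two-sided 5% test allows. The document does not support this. It speaks of comparisons between groups and nowhere proposes to claim efficacy from separate within-arm tests. It states no standardized change, and section 2.10 aims to keep background drugs and doses stable over the 12 weeks. Under literal random pairing of equal arms, the error rate stays near 5%.

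**Conclusion.** Wrong as written. The article assigns between-group comparisons of quantitative data to tests that need pairs, in a trial that has none. This follows from sections 2.2, 2.9 and 2.15 alone and needs no assumption.

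The size is limited. At a minimum the error affects baseline comparisons. On the likelier reading it also covers the echocardiographic measures, KCCQ, the toxin scale and walk distance taken as a quantity.

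A reader might infer that the trial's whole efficacy analysis is invalid. It is not: the main primary responder endpoint, the 110 per group and the event analyses stand. The p-value ranges rest on simulated normal data with 94 per arm. The 13% to 25% rests on an assumed equal change of 0.1 to 0.3 SD and illustrates why within-arm tests cannot stand in for the comparison; it is not a property of the stated plan.

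**What to change.** In section 2.15, replace the sentence on quantitative data with: *Between-group comparisons of quantitative data use the independent-samples t-test (or, for week-12 outcomes, an ANCOVA adjusted for the baseline value) or the Mann-Whitney U test.*

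Replace the ordinal sentence with: *Between-group comparisons of ordinal data use the Mann-Whitney U test. Paired t-tests and Wilcoxon signed-rank tests describe change within an arm only, and no efficacy claim rests on them.*

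It would help to say in the same place whether these rules apply to baseline characteristics, to outcomes or to both. Centre-adjusted models or centre-stratified rank tests are not needed to cure this error.

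The cost is two sentences of wording, with no change to sample size, visits, data collection or patients.
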